### Data collection methods

2.14

Study outcomes will be assessed at three time points: the baseline, 12th week and 18th week after the study's start. Table 2 provides an overview of data collection and outcome measures.

**TABLE 2 dom70414-tbl-0002:** GenOn Programme data collection and outcome measures.

	Baseline	12th week	18th week
Data collection			
Sociodemographic, clinical and health questionnaire	X		
Faecal collection	X	X	X
Blood collection	X	X	X
Blood pressure measurement	X	X	X
Anthropometric (weight, height, waist and hip circumference, sagittal diameter) and body composition assessment	X	X	X
Three‐day food records	X	X	X
Habitual Physical Activity Questionnaire	X	X	X
Three‐Factor Eating Questionnaire‐R21 and Power Food Scale	X	X	X
Chrononutrion (Night Eating Questionnaire and Morningness‐Eveningness Questionnaire) and sleep quality (Pittsburgh Sleep Quality Index)	X	X	X
Gastrointestinal Symptom Rating Scale and Bristol Scale	X	X	X
36‐Item Short Form Survey	X	X	X
Outcome measures			
Weight loss; difference in BMI, waist circumference and body composition		X	X
Dietary intake, dietary pattern, NOVA classification and plant‐based diet indices	X	X	X
Eating behaviour and hedonic hunger	X	X	X
Blood chemistry analysis (blood count, lipid profile, fasting blood glucose, glycated haemoglobin, kidney and liver function and markers of oxy‐inflammation, neuroendocrine control of satiety and intestinal permeability)	X	X	X
Genomic DNA analysis	X	X	X
Gene expression analysis	X	X	X
Faecal short‐chain fatty acids and faecal potential of hydrogen	X	X	X
Metagenomic analysis	X	X	X
Gut health	X	X	X
Physical activity	X	X	X
Eating behaviour and hedonic hunger	X	X	X
Quality of life	X	X	X

Abbreviation: BMI, body mass index.

### Blood pressure

2.15

Systolic and diastolic blood pressure will be measured using an automatic arm monitor (G‐Tech®, model BSP11, Accumed Medical‐Hospital Products Ltd., São Paulo, Brazil) with an accuracy of 3 mmHg. Blood pressure will be measured in both arms after a 5‐min rest period, and the measurement will be repeated in the arm showing the higher initial value.^30^ The result considered for analysis will be the mean of the last two readings and classified according to the cutoff points of the Brazilian Society of Hypertension.^31^

### Anthropometric measurements and body composition

2.16

Body weight and body composition will be determined using a tetrapolar electrical bioimpedance equipment (InBody, model 230, BiospaceCo. Ltd), following the clinical protocol: 10–12 h of fasting for solid foods, 4 h for liquids, no alcohol or physical exercise in the 24 h prior to the test, no caffeine intake and with an empty bladder.

Height will be measured using a wall‐mounted stadiometer (Seca, model 206, Hamburg, Germany). The BMI will be calculated as weight in kilogrammes divided by the square of the height, and overweight/obesity was classified according to the cutoff points of the WHO.^32^

Waist, hip, neck, arm, thigh and calf circumferences will be measured with a flexible and inelastic measuring tape, with an accuracy of 0.1 cm, following standardised recommendations. Waist circumference will be measured midway between the iliac crest and the last rib. The sagittal abdominal diameter will be measured with an abdominal calliper (Holtain Kahn Abdominal Calliper®) with a mobile shaft and 0.1 cm subdivision. The measurement will be taken at the point of the largest abdominal diameter.^33^ All anthropometric measurements will be taken in triplicate, and the average of the two closest values will be used as the final estimated measurement.

### Dietary intake

2.17

Data information from 24‐h food records completed into three sets of food records during the study (baseline, 12 and 18 weeks after the start of the study) will be entered into the Erica‐REC24h software.^34^ Proper recording of food and beverage intake, as well as estimating food portion sizes, will be explained to participants during the orientation session. The food diary must reflect all the food and beverages consumed by the participants within the specified periods, including the description of each food item (type, variety and brand name), amounts, the time of day the meal is taken and the cooking method (e.g., boiled, fried and broiled). The research team will verify and check the completeness and accuracy of the recorded intake. Total energy intake and nutrient consumption will be computed using the Nutritional Composition Tables of Foods Consumed in Brazil.^21^

The dietary pattern of individuals will be estimated using principal components factor analysis, which uses nutritional composition and food similarity to group foods.^35^, ^36^ Furthermore, the foods consumed by participants will be classified according to their degree of industrial processing, using the NOVA classification.^37^ Finally, food quality will be evaluated using three indices: the overall plant‐based diet index (PDI), the healthy plant‐based diet index (hPDI) and the unhealthy plant‐based diet index (uPDI).^38^, ^39^

### Serum and plasma biomarkers

2.18

After a 10‐ to 12‐h fast, blood samples will be collected at the specified time points (baseline, 12 and 18 weeks after the start of the study). A trained nursing team will collect approximately 30 mL of blood for analysis of complete blood count, lipid profile, fasting blood glucose, glycated haemoglobin, kidney and liver function and markers of oxidative stress, inflammation, neuroendocrine control of satiety and intestinal permeability.

### Genomic DNA and gene expression analysis

2.19

Genomic DNA will be extracted from peripheral blood cells using commercial DNA extraction kits. After obtaining the DNA, its concentration and purity will be determined spectrophotometrically. Total DNA methylation analysis will be performed using a commercial kit according to the manufacturer's recommendations.

Gene expression will be performed by extracting RNA from peripheral blood mononuclear cells ‐ PBMC using TRIzol® reagent (Invitrogen™) according to the manufacturer's recommendations. After RNA extraction, its concentration and purity will be determined spectrophotometrically. For retrotranscription, RNA aliquots will be standardised to 2 ng/μL. Ten microliters of sample will be added to 10 μL of master mix (2 μL of buffer solution, 0.8 μL of deoxynucleotide triphosphates (dNTP), 2 μL of random primers, 1 μL of reverse transcriptase, 1 μL of RNAse inhibitor and 3.2 μL of ultrapure water) and then incubated in a thermocycler at 25°C for 10 min, 37°C for 120 min, 85°C for 5 min, followed by cooling to 4°C. After double‐strand synthesis from total RNA, the complementary DNA (cDNA) concentrations of each sample will be determined spectrophotometrically and adjusted to the same concentration. For micro‐RNA (miRNA) analysis, 20 ng of total RNA will be reverse transcribed using the reverse transcription kit according to the manufacturer's protocol and the miRNA‐specific reverse transcription primers provided with the TaqMan MicroRNA Assay (Life Technologies). The miRNA‐specific cDNA will be amplified in triplicate with the PCR master mix and the respective manufacturer‐specific probe. The expression of genes and miRNA involved in cardiometabolic risk, inflammation, satiety and/or those modulated by nutritional intervention will be evaluated using a thermocycler. Gene expression levels will be assessed and normalised using *GAPDH* as an internal control following previously described protocols.^40^, ^41^ The fold change (2‐ddCt) in target genes, normalised to *GAPDH* and relative to the lowest expression profile, will be calculated for each sample according to the manufacturer's guidelines.

### Faecal short‐chain fatty acids and faecal potential of hydrogen (pH)

2.20

Short‐chain fatty acids (SCFA) in faeces will be determined by high‐performance liquid chromatography (HPLC) after a cold extraction protocol.^42^ Faecal pH will be determined using a pH metre after dilution and homogenisation of faeces in ultrapure water.^43^

### Metagenomic analysis

2.21

Total genomic DNA will be extracted from stool samples (300 mg) following a mechanical disruption (shaking and impact) and phenol/chloroform extraction protocol.^44^ Amplicons of the 16S rRNA V3‐V4 region will be generated using forward primer 341F (5′‐CCTAYGGGRBGCASCAG‐3′) and reverse primer 806R (5′‐GGACTACNNGGGTATCTAAT‐3′) and a barcoded primer set adapter for the Illumina NovaSeq platform (Illumina, San Diego, CA, USA).^44^ Samples will be loaded onto an Illumina flow cell for paired‐end sequencing reactions using the Illumina NovaSeq PE250 platform at Novogene Corporation on the University of California, Davis campus (Sacramento, CA, USA). Amplicons will be sequenced in a 2 × 250 bp NovaSeq run, using custom primers and sequencing procedures.^45^ Sequences obtained for all samples will be submitted to the Sequence Read Archive (SRA) database at the National Center for Biotechnology Information (NCBI) (http://www.ncbi.nlm.nih.gov/sra) under accession number PRJNA860372. Data processing and analysis will be performed using Mothur software v.1.44.3.^46^ Paired‐end sequences will be clustered into operational taxonomic units (OTUs). Each OTU represents a genetically unique group of biological organisms, and a sequence similarity cutoff point of 97% was adopted. The taxonomic classification of OTUs will be performed based on the SILVA v.138 database. The samples will be grouped according to the experimental groups and intervention times.

### Eating behaviour and hedonic hunger

2.22

The Three‐Factor Eating Questionnaire‐R21 (TFEQ‐21)^47^ will evaluate the eating behaviour of the participants, and to assess hedonic hunger, the Power Food Scale^48^ will be used.

### Gut health

2.23

The Gastrointestinal Symptom Rating Scale^49^ and the Bristol Scale^50^ will be used to evaluate participants' gut health.

### Physical activity

2.24

The Habitual Physical Activity Questionnaire^51^ will be used to measure the level of physical activity of the participants.

### Chrononutrion and sleep quality

2.25

The Night Eating Questionnaire^52^ and the Morningness‐Eveningness Questionnaire^53^ will be used to assess chrononutrition, and sleep quality will be assessed by the Pittsburgh Sleep Quality Index.^54^

### Quality of life

2.26

The 36‐Item Short Form Survey (SF‐36)^55^ is an essential tool for assessing quality of life, with higher scores indicating better health.

### Data handling and quality

2.27

The entire team involved in collecting data for this study will receive specific training and have prior experience in the field. The study's progress, protocol compliance, data validity and integrity and ethical considerations will be periodically assessed by a clinical trial monitor. Participants will be instructed to answer questions truthfully. An intention‐to‐treat (ITT) analysis will be used to include data from individuals who withdraw from the study for any reason. All participants will be followed for 18 weeks after treatment assignment.

After the questionnaires are administered, the responses will be checked for completeness and consistency. To ensure accurate data entry, two operators will enter the data independently, and the data entry system will feature pre‐programmed logic check functions to minimise transcription errors.

A unique numeric code will identify each participant. All data will be archived at the institution and accessible exclusively to the research team. Information from the questionnaires and consent forms will be kept in printed format, stored separately from other study data and identified by a specific numeric code.

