### Sample size calculation

2.7

For a sample calculation, analyses were performed assuming a weight loss of 5%–10% as the primary outcome, a significance level of 5%, a test power of 90% and an effect size of 0.50. Thus, considering a 30% sample loss, the sample size is 30 per group, totalling 120 participants. The G*Power 3.0.10 analysis programme was used, adopting an ‘a priori’ analysis using the variance test (ANOVA) for repeated measures.

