### Statistical analysis

2.28

Statistical analyses will be performed using SPSS software, version 24.0 (SPSS Inc., Chicago, IL, USA). Quantitative variables will be expressed as mean ± standard deviation (SD) or median (with 25th–75th percentiles), whereas qualitative variables will be presented as frequencies (percentages). Data normality will be assessed using the Kolmogorov–Smirnov test, and logarithmic transformation will be applied when distributions deviate from normality. Baseline differences between groups will be examined using the chi‐square test for qualitative variables and the independent‐samples Student's *t*‐test for quantitative variables.

A mixed ANOVA will be applied to determine the effects of groups (control low‐risk group; control high‐risk group, intervention low‐risk group, intervention high‐risk group), time (baseline, 12 weeks and 18 weeks) and genotype (LR and HR). Effect sizes will be calculated as partial eta‐squared (*ηp*
^2^), classified as small (0.01–0.05), moderate (0.06–0.13) or large (≥0.14).^56^ Bonferroni‐adjusted estimated marginal means will be used for post hoc comparisons. Variables violating homogeneity assumptions serão log10‐transformed. One‐way ANOVA will be used to compare changes in the evaluated variables between the control and intervention groups.

Linear and nonlinear regression models will be explored to estimate the association between variables with significant correlation. The statistical significance criterion will be *p* ≤ 0.05.

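### The named ANOVAs cannot deliver the promised intention-to-treat analysis unless missing weights are handled first, and no method for that is named

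*Protocol article*

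**What the plan says.** - **Analysis population (section 2.27).** The plan commits to intention to treat, an approach whose "analysis will be used to include data from individuals who withdraw from the study for any reason". The same section adds: "All participants will be followed for 18 weeks after treatment assignment".
- **Methods (section 2.28).** "Statistical analyses will be performed using SPSS software, version 24.0". "A mixed ANOVA will be applied to determine the effects of groups", time and genotype, with baseline, week 12 and week 18 as the time levels. Results are to be given as partial eta-squared with Bonferroni-corrected marginal means. In addition, a one-way "ANOVA will be used to compare changes in the evaluated variables between the control and intervention groups". No imputation, likelihood-based model or other treatment of missing values is mentioned.
- **Expected loss (section 2.7).** The total of 120, at 30 per group, was reached "considering a 30% sample loss".
- **Removal from the study (section 2.13).** Participants who do not keep to the eating plan, or whose attendance falls below 75%, are discontinued from the study in either arm. A lapse in granola and high-protein breakfast, or a lasting granola-related adverse event, also leads to discontinuation. These last two can arise only in the satiety arm.

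**The concern.** The article fixes both an analysis principle and an analysis method, and the two do not fit together. A classical mixed ANOVA, which the listed outputs point to in SPSS, needs a complete set of visits for each person and by default deletes anyone with a gap. A participant weighed at baseline and week 12 but not at week 18 then contributes nothing to it, and the week-12 weight is discarded. A change score likewise cannot be formed without the follow-up weight.

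The population analysed would therefore be defined by what happened after randomisation. That matters here for two reasons: the plan expects substantial loss, and its own discontinuation criteria tie loss to adherence, with extra routes out in one arm. If people with poorer weight loss leave more often, and more of them leave from one arm, a comparison of completers no longer compares the groups as randomised.

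**Working it through.** **1. How many would be excluded.** Inputs are the 120 participants and 30% loss in section 2.7. Assume that each lost participant misses at least one visit and that nothing is imputed.
- Excluded: 0.30 × 120 = 36.
- Retained: 120 − 36 = 84, or 21 per group if loss is even.
- At an assumed 10% or 20% loss, 108 or 96 are retained.

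**2. Is power the harm?** Section 2.7 gives "a significance level of 5%, a test power of 90% and an effect size of 0.50". The metric, the correlation between visits and the effect tested are not stated. Taking 0.50 as Cohen's f, an assumed correlation of 0.5, four groups and three visits, the between-groups noncentrality is λ = N·f²·m / [1 + (m − 1)ρ].
- The plan's own figure is not reproduced. This test needs 42 participants for 90% power (44 when balanced), which is 63 after dividing 44 by 0.7. This mismatch does not decide the present point.
- With 84 completers, λ = 84 × 0.25 × 3 / 2 = 31.5 on 3 and 80 degrees of freedom, and power is 99.8%.
- If the effect were f = 0.25, power would be 80% with 120 and 62% with 84.

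At the stated effect size, read as f, power is not the issue.

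**3. How large could the bias be?** The documents give no SD, correlation or dropout model, so every input here is an assumption: 60 per arm, no true effect, SD 4.5 percentage points of weight change, week-12 to week-18 correlation 0.85, and dropout more likely with poorer week-12 weight loss. There were 4,000 simulated trials per scenario, so Monte Carlo error is about 0.94/√4000 = 0.015. Negative values favour satiety.

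| Loss, control v satiety | Timing | Completers bias | Likelihood bias |
|---|---|---|---|
| Equal (30% or 33.5% each) | after week 12 | about 0 | about 0 |
| 29% v 38% | after week 12 | −0.08 to −0.28 | within 0.03 of 0 |
| 20% v 40% | after week 12 | up to −0.61 | within 0.03 of 0 |
| 29% v 38% | half before week 12 | not tabulated | −0.07 |
| 29% v 38% | all before week 12 | −0.22 | −0.22 |

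The range in the second row comes from weak to strong dependence of dropout on week-12 weight loss (log-odds 0.3 to 1.0 per SD). The last two rows use 0.8. The 29% v 38% split averages 33.5%, or about 40 of 120, slightly more than the planned 36.

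**4. Effect on error rate.** In the strong 29% v 38% case the bias is 0.275 against an empirical standard error of 0.938, so 0.275/0.938 = 0.29 standard errors. Two-sided type I error becomes P(Z > 1.67) + P(Z < −2.25), about 6.0% instead of 5%. At −0.61 with a similar standard error, the shift is 0.65 standard errors and P(Z > 1.31) + P(Z < −2.61) is about 10%.

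**5. Precision.** When loss falls after week 12, using the week-12 weights lowered the variance by about 14% to 24%. That is worth 1/0.86 = 1.16 to 1/0.76 = 1.32 times the participants. When all loss falls before week 12, there is no gain.

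**The case against.** The strongest reply is that section 2.28 never says incomplete cases are dropped. Imputing missing weights before the same ANOVA would honour the intention-to-treat statement, and such detail often sits in a full protocol or analysis plan that is not shown here. This stands as far as it goes. A reader might infer that the primary result will be a completers analysis with 30% excluded; the documents do not say so. That result follows from the named method only if nothing is added. The 30% is a planning allowance, and anyone who withdraws but is still weighed, as section 2.27 implies, stays in the ANOVA.

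A reader might also infer that section 2.13 guarantees unequal loss and a definite bias toward satiety. It does not. Non-adherence to the eating plan and low attendance apply to both arms, and withdrawal from the control arm could offset the satiety-only criteria. With equal loss and the same mechanism in both arms, the bias vanishes.

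Finally, a likelihood model is no cure for early loss driven by weight change that was never observed, as the last row of the table shows. The reply leaves the mismatch itself in place: the article commits to a principle and to methods that cannot meet it unaided, and names nothing to join them.

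**Conclusion.** The point holds in conditional form. The intention-to-treat commitment cannot be met by the named ANOVAs unless missing values are handled first. If the planned 30% loss occurs and nothing is imputed, the mixed ANOVA would exclude about 36 of 120 and keep 84. Loss may be informative and unequal because section 2.13 links it to adherence and adds criteria that only the satiety arm can meet.

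Under the assumed dropout models the completers bias ranges from about zero with equal loss to a few tenths of a percentage point or somewhat more toward satiety with unequal loss. Neither its size nor the advantage of a likelihood analysis is established by the documents, since both depend on how unequal and how late the loss is. The main harm is selection bias in the primary comparison, not power at the stated effect size.

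Section 2.13, which discontinues people from the study, also conflicts with the statement in section 2.27 that everyone is followed for 18 weeks. How much data is missing turns on which of the two is meant.

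**What to change.** 1. **Primary analysis.** Use a likelihood-based linear mixed model for repeated measures (SPSS MIXED, unstructured covariance) on all available weights of all randomised participants, each in the assigned arm. Either keep baseline as an outcome visit, or use it as a covariate together with multiple imputation, so that those lost before week 12 are included. Multiple imputation before the planned ANOVA is an acceptable alternative.
2. **Sensitivity analysis.** Add one for informative loss, for example assuming that those lost return toward baseline weight.
3. **Completers ANOVA.** Keep it as supportive only.
4. **Reconcile sections 2.13 and 2.27.** State whether participants discontinued from the study are still measured to week 18. This needs settling while follow-up is running, because weights not collected cannot be recovered later.

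The cost is small: revised analysis wording, a different procedure in the same software and slightly more analysis work. With the mixed model, partial eta-squared gives way to mean differences with confidence intervals.

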### Statistical analysis

2.28

Statistical analyses will be performed using SPSS software, version 24.0 (SPSS Inc., Chicago, IL, USA). Quantitative variables will be expressed as mean ± standard deviation (SD) or median (with 25th–75th percentiles), whereas qualitative variables will be presented as frequencies (percentages). Data normality will be assessed using the Kolmogorov–Smirnov test, and logarithmic transformation will be applied when distributions deviate from normality. Baseline differences between groups will be examined using the chi‐square test for qualitative variables and the independent‐samples Student's *t*‐test for quantitative variables.

A mixed ANOVA will be applied to determine the effects of groups (control low‐risk group; control high‐risk group, intervention low‐risk group, intervention high‐risk group), time (baseline, 12 weeks and 18 weeks) and genotype (LR and HR). Effect sizes will be calculated as partial eta‐squared (*ηp*
^2^), classified as small (0.01–0.05), moderate (0.06–0.13) or large (≥0.14).^56^ Bonferroni‐adjusted estimated marginal means will be used for post hoc comparisons. Variables violating homogeneity assumptions serão log10‐transformed. One‐way ANOVA will be used to compare changes in the evaluated variables between the control and intervention groups.

Linear and nonlinear regression models will be explored to estimate the association between variables with significant correlation. The statistical significance criterion will be *p* ≤ 0.05.

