### Outcomes

2.6

The primary clinical outcome will be estimated weight loss of 5%–10% of initial body weight, resulting in corresponding changes in BMI, waist circumference and body composition. Secondary outcomes will include improvements in indicators of quality of life, self‐esteem and quality of food intake, as well as serum cardiometabolic, oxy‐inflammatory, epigenetic, satiety and intestinal permeability markers.

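### Two tests on the trial's own data decide whether an outcome is log-transformed, so the scale of the primary weight analysis is not fixed in advance, and the rule is not confined to variables whose log exists

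*Protocol article*

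**What the plan says.** Section 2.28 of the protocol article sets two conditions under which a variable is logged.

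- **Normality.** "Data normality will be assessed using the Kolmogorov–Smirnov test", and "logarithmic transformation will be applied when distributions deviate from normality".
- **Homogeneity.** A later sentence, partly left in Portuguese, begins "Variables violating homogeneity assumptions serão log10" and prescribes a log10 transformation.

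Both are worded for variables in general. Neither names the outcomes it covers, excludes any outcome, or says what happens if the log cannot be taken or does not help.

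The section uses two kinds of model. A mixed ANOVA covers group, time (baseline, 12 and 18 weeks) and genotype. The sentence directly after the homogeneity rule adds a one-way "ANOVA will be used to compare changes in the evaluated variables between the control and intervention groups".

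The primary outcome is worded as a change. Section 2.6 says "The primary clinical outcome will be estimated weight loss of 5%–10% of initial body weight". Table 2 in section 2.14 lists, for weeks 12 and 18 only, "Weight loss; difference in BMI, waist circumference and body composition".

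**The concern.** An analysis scale should be settled before the outcome data are seen, because it determines what is estimated. Untransformed weight gives a difference in kilograms or percentage points. Logged weight gives a ratio of geometric means. Here that choice is handed to two significance checks on the trial's own data, and the primary outcome is not exempted.

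The rules also have no stated domain. A log exists only for positive numbers. Measured weight and most serum markers qualify, but changes do not, since they can be zero or of either sign. The section analyses changes and places no limit on the log rule. An analyst following the wording could therefore meet a variable to which it cannot be applied. The ways out, dropping participants or adding a constant, are not prespecified. Dropping participants would also sit badly with the intention-to-treat analysis promised in section 2.27.

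**Working it through.** The plan gives no figure to reproduce on this point. The check has three parts.

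**1. What fixes the scale**

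| Element | What section 2.28 states | What it leaves open |
|---|---|---|
| Normality trigger | Kolmogorov–Smirnov | measured values or residuals; pooled or by group; which visit; threshold |
| Homogeneity trigger | log10 if violated | which test; threshold |
| Scope | variables in general | whether weight or change variables are exempt |
| If the log fails or does not help | nothing | all of it |

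How the test is run matters. In simulation at n = 30 per group, lognormal data (log SD 0.5) are flagged roughly half the time if the test allows for the estimated mean and SD (Lilliefors correction), and about 3% to 4% of the time if it does not. If each of the 4 × 3 = 12 group-by-visit cells were tested at 5% and treated as independent, the chance of at least one false flag on normal data would be 1 − 0.95^12 = 46%. The same data can therefore end up on either scale.

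**2. Where the log exists**

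- Measured weight is always positive, so its log is always defined in the mixed ANOVA.
- For weight loss as baseline minus follow-up, the log is undefined for anyone with a loss of zero or less.
- For change as follow-up minus baseline, it is undefined for everyone who loses weight or stays the same. The article does not state a sign convention.

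**3. How many participants would have no defined log if losses were logged**

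The documents give no SD for weight change. Assume a normal loss with mean μ and SD σ, in percent of initial weight. Then P(loss ≤ 0) = Φ(−μ/σ).

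| Mean loss | SD 3 | SD 4 | SD 5 |
|---|---|---|---|
| 3% | Φ(−1.00) = 15.9% | Φ(−0.75) = 22.7% | Φ(−0.60) = 27.4% |
| 5% | Φ(−1.67) = 4.8% | Φ(−1.25) = 10.6% | Φ(−1.00) = 15.9% |
| 7% | Φ(−2.33) = 1.0% | Φ(−1.75) = 4.0% | Φ(−1.40) = 8.1% |

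The range is 1.0% to 27.4%, or about 1 to 33 of 120 participants (120 × 0.0098 = 1.2; 120 × 0.274 = 32.9). The 3% row lies below the 5%–10% loss that section 2.6 names. At a mean of 10%, the top of that range, the share is 0.04% with SD 3 and 4.8% with SD 6.

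**The case against.** **The text never says that change scores are logged.** This is correct. The normality rule stands in the opening paragraph, beside descriptive statistics and baseline comparisons. The main model works on measured values at each visit, and section 2.7 sizes the trial on a repeated-measures ANOVA. Logging measured weight is an open and well-defined reading. A reader might infer that the plan commits the trial to logging weight loss and losing the non-responders, but the document does not support that. What stands is narrower: the rule has no stated limit, and a change analysis sits next to it.

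**For weight, the change of scale is mild.** This is partly right. A within-person difference in log weight is close to a percentage change: a 5% loss gives −ln(0.95) = 0.051, and a 10% loss gives −ln(0.90) = 0.105. Such an analysis stays near the percentage wording of section 2.6. It is still a different quantity from a difference in kilograms, and which one is reported would depend on the data.

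**A stronger claim about bias is tempting.** A reader might infer that the rule would shrink the difference between diets by a calculable amount, or that a real diet effect would itself trigger the log. Neither is supported. Any shrinkage worked out from normal losses describes data that the normality test seldom flags. With 60 per arm, means of 5% and 3% and SD 4, a pooled test with the Lilliefors correction rejects in about 4% to 5% of simulated trials, no more often than with no diet effect. The direction of any bias also depends on the unstated sign convention.

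**A condensed article leaves such detail to an analysis plan.** This is fair for the choice of residuals or measured values, and for the list of biomarkers. It does not cover the rule itself, which the article states as what will be done, without exception.

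**Conclusion.** The point holds in a limited form. Section 2.28 makes the scale of every outcome, including the primary weight outcome, depend on a normality test and a homogeneity check on the trial's own data. That follows from the text alone and needs no assumption.

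The second part is conditional. The rules are not confined to variables that have a log. If they were applied to weight loss, about 1% to 27% of participants would have no defined value, assuming a normal loss with mean 3% to 7% and SD 3 to 5 points. Those inputs are illustrative. How often either rule would trigger for weight cannot be said from the documents, so no size of bias or loss of power is claimed.

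This should be corrected before the data are analysed. It does not show that the planned comparison is invalid.

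**What to change.** - Delete both test-triggered rules: the one tied to Kolmogorov–Smirnov and the one tied to homogeneity. Removing only the first would leave the scale data-dependent.
- State that weight is analysed untransformed, as kilograms or as percentage change (choose one), with baseline weight as covariate.
- Use residual plots or robust standard errors as a check on that model only, not as a way to choose the scale.
- Name in advance the strictly positive, skewed biomarkers to be analysed as logged measured values with log baseline as covariate, reported as ratios of geometric means.
- State that change scores are not logged.

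The cost is a change of wording in the analysis section. Data collection, sample size and trial conduct are unaffected.
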